### Treatment and trial procedures

Systemic chemotherapy will be administered outside of the trial as per local standard (Fig. 1).

**Fig. 1 Fig1:**
[figure not shown]
ACTICCA-2 trial design. *CCA*: cholangiocarcinoma, *MDT*: multidisciplinary team, *RFA*: radiofrequency ablation, *SEMS*: self-expanding metal stent, *OS*: overall survival, *QoL*: quality of life

As per study protocol, the selection of the RFA device is up to the discretion of the investigator, given approval in this context. The device provides bipolar energy to perform partial or complete ablation of tissue in the biliary tract. The RFA procedure will be performed only once at the beginning of the study. The extent of RFA for each individual patient will be decided by the investigator during the procedure. Of importance, trial site is one of the stratification criteria for randomization of patients to account for a possible procedure-related effects. Subsequent stent replacements will be carried out without additional RFA regardless of patient randomization to the intervention or control group.

All patients in the trial will receive endoscopic stenting and palliative chemotherapy as SOC as is indicated by local standards and as recommended in current guidelines [2]. Patients receiving liver-directed local therapy for hilar lesions, such as internal or external radiation therapy or chemosaturation will be censored at time of treatment if already enrolled in the trial. Radiation therapy to distant tumor sites (e.g. bone) is allowed. There are no restrictions on medications or other treatments, including full access to palliative care and symptom management (including pain control) throughout the trial.

### Arm A (intraductal RFA plus biliary stenting)

Patients assigned to the study arm will receive systemic treatment and bile duct stenting with plastic or metallic stents with intraductal RFA of malignant bile duct obstructions employing a CE-certified RFA-catheter prior to stent placement. RFA will be applied once.

### Arm B (control: biliary stenting alone)

Patients assigned to the control arm will receive systemic treatment and bile duct stenting with plastic or metallic stents alone.

### Assessments for screening, treatment and follow-up

An overview of trial assessment is displayed in Table 2.

**Table 2 Tab2:** Overall study schedule overview

		STUDY PERIOD				
		Screening/ Enrollment	Randomization, Allocation + Visit 1	Post-allocation		
				Visit 2	Visit 3	Follow-up
Timepoint		-3–0 weeks	0	3 months (± 2 weeks)	6 months (± 2 weeks)	q3 months (± 2 weeks)
ENROLMENT:	Eligibility screen	X				
	Informed consent	X				
	Medical history (a)	X				
	Lab tests (b)	X	X	X	X	
INTERVENTIONS:	ERCP + stent		X	X (c)	X (c)	
	ERCP + stent + RFA (d)		X			
ASSESSMENTS:	Assessment primary endpoint (e)			X	X	
	Safety (f)		X	X	X	
	QoL (g)		X	X	X	
	Clinical event rate @ 6 months (h)				X	
	Cumulative days of overnight-hospital stays				X	
	Systemic therapy (i)		X	X	X	
	Survival status			X	X	X (k)

^a)^ Demographic data, baseline tumor data, concomitant diseases, current medication, prior endoscopic procedures

^b)^ CBC, INR, GGT, AP, AST, ALT, bilirubin total and direct, creatinine, Sodium, Potassium, CRP

^c)^ Only in patients who did not experience primary endpoint until then

^d)^ Only in patients randomized in the study group

^e)^ Time-to-first event (for 6 months follow up), i.e. stent dysfunction defined by bilirubin > 5 mg/dl and/or cholangitis

^f)^ Terminology and grading according to NCI CTCAE v5

^g)^ EORTC QLQ-C30 and EORTC QLQ-BIL21

^h)^ Cumulative rate of clinical events @ 6 months, such as stent dysfunction defined by bilirubin > 5 mg/dl and/or cholangitis

^i)^ Data collection regarding administration and complications of systemic therapy (administered as SOC)

^k)^ Per telephone contact

#### Screening

Within 3 weeks prior to randomization/start of first treatment (i.e. stenting with or without RFA) the following will be assessed/obtained:

Signed written informed consent.Medical history including previous cancer history, cancer treatment, concomitant diseases, current medication, prior endoscopic procedures.Demographics.ECOG performance status.Laboratory tests: Hematology panel (hemoglobin, platelets, WBC and WBC differential with neutrophils, lymphocytes, monocytes) chemistry panel (sodium, potassium, calcium, creatinine, total and direct bilirubin, alkaline phosphatase, 𝛾GT, ALT, AST, CrP, INR, aPTT, PT) and CA 19 − 9, CEA (optional).

#### Randomization and treatment (visit 1)

After enrolment, patients will be randomized (1:1) to either receive intraductal RFA followed by bile duct stenting or bile duct stenting alone. Additionally, the following will be assessed for baseline:

Laboratory tests as shown above (only if screening lab values are > 7 days old).Safety (terminology and grading according to NCI CTCAE v5 [see suppl. material])Data collection regarding administration and complications of systemic therapy (administered as SOC).Quality of life (QoL) assessment using the European Organisation for Research and Treatment of Cancer (EORTC) questionnaire QLQ-C30 [see suppl. material Fig. 1] and the module BIL21 [see suppl. material Fig. 2].

#### Visit 2 & 3

The following will be assessed at three and six months (each +/- 2 weeks) after randomization:

Laboratory tests as shown above.ERCP and stent replacement (within regular clinical management of the patients), not mandatory for patients who have experienced the primary endpoint of stent dysfunction, resulting in a change of timeline regarding stent replacement.Safety, data collection regarding administration and complications of systemic therapy (SOC), QoL, days of overnight hospital stays, and survival status.

#### Survival follow-up

Following Visit 3, every three months (+/- 2 weeks), the survival status will be assessed remotely, e.g., via telephone contact, until the end of the study.

### Endpoint definition

The primary endpoint is time to first event, i.e. stent dysfunction defined by bilirubin > 5 mg/dl and/or cholangitis (fever > 38.5 °C and/or increase in C-reactive protein (CrP) by at least 3-fold upper limit of normal and at least 20% from baseline without extrahepatic focus and absence of tumor progression) leading to premature stent replacement and/or disruption of chemotherapy. This endpoint is clinically relevant and paramount for the management of patients with perihilar and/or ductal CCA and represents a generally agreed core outcome for this population. Because systemic treatment discontinuation due to biliary complications is so critical for these patients, these endpoints are proposed by current guidelines as surrogates for survival [2]. According to recently published studies on this topic, the event rate at 6 months in the control group is estimated to be 50% [14, 20]. Our study aims to detect a clinically relevant reduction of the rate by 50% in the RFA group to 25%, resulting in a number needed to treat (NNT) of 4. This event reduction has to be achieved in the setting of palliative systemic therapy and seems reasonable considering the previously reported beneficiary effects of RFA on stent patency and OS [7, 9, 14, 20]. Importantly, all possible events will be reviewed by a blinded and independent endpoint-review committee (ERC), leading to a prospective randomized open blinded endpoint (PROBE) design.

The secondary endpoints will include OS, QoL, clinical event rate at 6 months, total days of over-night-hospital-stays during the trial period as well as safety (terminology and grading according to NCI CTCAE v5). Median OS will be calculated as a secondary outcome to generate data for larger clinical trials targeting OS as a primary endpoint. Following the fixed study follow-up period of 6 months, patients or primary care providers will be contacted every 3 months by telephone call. QoL will be assessed with EORTC QLQ-C30 [suppl. material Fig. 1] and EORTC QLQ-BIL21 [suppl. material Fig. 2] questionnaires at each of the three on-site study visits. Clinical events as defined by the primary endpoint, i.e. stent dysfunction leading to premature stent replacement and/or disruption of chemotherapy, will be counted at 6 months follow-up and reported as a time-independent clinical event rate. In addition, cumulative over-night-hospital-stays within the fixed 6 months follow-up period will be counted. Moreover, assessing the safety of intraductal RFA is a major aim of the study and will be investigated as a secondary endpoint. RFA-related events will be examined, documented, and graded according to NCI CTCAE v5.

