**Methods/Design:**

ACTICCA-2 is a multicenter, randomized, controlled, open-label, investigator-initiated trial. 120 patients with perihilar or ductal CCA with indication for biliary stenting and systemic therapy will be randomized 1:1 to receive either RFA plus bile duct stenting (interventional arm) or bile duct stenting alone (control arm). Patients will be stratified by trial site and tumor location (perihilar vs. ductal). Both arms receive palliative systemic treatment according to the local standard of care determined by a multidisciplinary tumorboard. The primary endpoint is time to first biliary event, which is determined by an increase of bilirubin to > 5 mg/dl and/or the occurrence of cholangitis leading to premature stent replacement and/or disruption of chemotherapy. Secondary endpoints include overall survival, safety according to NCI CTCAE v5, quality of life assessed by questionnaires (EORTC QLQ-C30 and QLQ-BIL21), clinical event rate at 6 months after RFA and total days of over-night stays in hospital. Follow-up for the primary endpoint will be 6 months, while survival assessment will be continued until end of study (maximum follow-up 30 month). All patients who are randomized and who underwent endoscopic stenting will be used for the primary endpoint analysis which will be conducted using a cause-specific Cox proportional hazards model with a frailty for trial site and fixed effects for the treatment group, tumor location, and stent material.

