### Patient selection and randomization

Patients will be enrolled into the trial according to the eligibility criteria (Table 1). Inclusion and exclusion criteria are based on the main selection criteria for patients with unresectable perihilar and/or ductal CCA who are recommended to receive bile duct stenting and palliative systemic therapy by current guidelines [2]. In detail, these criteria reflect the patient’s clinical status including potential safety concerns regarding the endoscopic intervention and administration of systemic chemotherapy. Performance status 0–1 according to the Eastern Cooperative Oncology Group (ECOG) is a well-established cut-off for the eligibility of patients to receive systemic therapy and invasive procedures, such as endoscopic retrograde cholangiopancreatography (ERCP). Patients will be excluded if prior RFA and/or multiple stenting for CCA has been performed during the past 3 months to rule out competing effects on the outcome analysis (first stent replacement or placement of the first stent for tumor-related bile duct obstruction within 3 months prior to study inclusion is allowed). Patients with concomitant diseases or malignancies with limited prognosis or high likelihood of study discontinuation (e.g. severe or uncontrolled cardiovascular disease, such as congestive heart failure New York Heart Association (NYHA) III or IV, unstable angina pectoris, myocardial infarction within ≤ 3 months, and/or significant arrhythmias) will be excluded. This is in line with clinical eligibility criteria for the administration of bile duct stenting and subsequent administration of systemic therapy. Taken together and considering a relatively large sample size and a multicenter study design, the study population is representative, and results are generalizable to the target population of interest.

**Table 1 Tab1:** Eligibility criteria for the ACTICCA-2 enrollment phase

Unresectable perihilar and/or ductal CCA with indication for bile duct stenting
Signed written informed consent
ECOG performance status 0–1
Age ≥ 18 years
Eligibility for palliative systemic therapy based on clinical and laboratory parameters (except hyperbilirubinemia) as determined by the local MDT
No prior RFA for CCA
No repeated bile duct stenting for > 3 months (trial inclusion is possible upon first stent replacement or initial stent placement)

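### The primary endpoint is worded in three non-identical ways, and jaundice already present at entry counts as stent dysfunction under some of them and not under others

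*Protocol article*

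**What the plan says.** All references are to the protocol article.

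- **Abstract, Methods/Design.** The wording here: "which is determined by an increase of bilirubin to > 5 mg/dl and/or the occurrence of cholangitis leading to premature stent replacement". Interrupted chemotherapy is named as the other possible consequence. Bilirubin must rise, but the value from which the rise is measured is not stated.
- **Endpoint definition.** The event is "time to first event, i.e. stent dysfunction defined by bilirubin > 5 mg/dl and/or cholangitis", followed by "leading to premature stent replacement and/or disruption of chemotherapy". Bilirubin is a bare level here. In the same sentence the C-reactive protein criterion is tied to the starting value: "and at least 20% from baseline without extrahepatic focus and absence of tumor progression".
- **Table 2, footnote e (primary endpoint).** "Time-to-first event (for 6 months follow up), i.e. stent dysfunction defined by bilirubin > 5 mg/dl and/or cholangitis". No consequence is required.
- **Table 2, footnote h (event rate).** "Cumulative rate of clinical events @ 6 months, such as stent dysfunction defined by bilirubin > 5 mg/dl and/or cholangitis". Again there is no consequence, although the text on secondary endpoints under Endpoint definition keeps the clause for this same rate.
- **Table 1, eligibility.** "Eligibility for palliative systemic therapy based on clinical and laboratory parameters (except hyperbilirubinemia) as determined by the local MDT". No upper bilirubin limit is given, and patients may enter at initial stent placement or at first stent replacement.
- **Patient selection and randomization.** Randomization and the procedure take place on the same day.
- **Sample size calculation and statistical analysis.** The primary endpoint is the only confirmatory analysis.

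**The concern.** Patients enter with an indication for bile duct stenting, some of them with raised bilirubin, and time zero falls before drainage can have lowered it. A level-only criterion can therefore be met by the jaundice that led to enrolment, with no loss of stent function after the index procedure. The endpoint is time to first event, so a patient counted in this way contributes nothing further, and a later true stent failure goes unrecorded. If such events are about equally common in both arms, they dilute the treatment contrast.

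Separately, the three wordings can classify the same patient differently, and the trial has one confirmatory test that depends on that classification.

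**Working it through.** **1. The wordings side by side.** Each row is a type of patient and each cell says whether the event counts. The consequence is early stent replacement or disrupted chemotherapy. The table assumes that the consequence clause covers bilirubin as well as cholangitis.

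| Patient | Abstract | Endpoint definition | Table 2 (e) |
|---|---|---|---|
| Above 5 mg/dl at entry, falling but still above 5, no consequence | No | No | Yes |
| Same, but chemotherapy disrupted or stent replaced early because of it | No (not an increase) | Yes | Yes |
| Falls to 5 or below, rises above 5 again, no consequence | No | No | Yes |
| Falls to 5 or below, rises above 5 again, with consequence | Yes | Yes | Yes |

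The wordings agree only in the last row. The sentence structure also allows a reading in which the clause attaches to cholangitis alone. On that reading, row 1 becomes an event under Endpoint definition, and row 3 becomes one under both the abstract and Endpoint definition. The article also does not say whether a delayed start of chemotherapy counts as disruption.

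**2. The stated design.** Inputs from the sample size section: 6-month event rates of 50% and 25%, two-sided 5% level, 80% power, 2.5% loss, 60 per arm.

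- Hazard ratio: ln(0.75)/ln(0.50) = 0.415, as stated.
- Two proportions: 58 per arm = 116; 116/0.975 = 119.
- Mean event probability: (0.50 + 0.25)/2 = 0.375. Freedman: 46 events, 46/0.375 = 123 before loss. Schoenfeld: 41 events, 41/0.375 = 110 before loss.
- Log-rank calculation of the Lakatos type with 2.5% loss: 116 patients needed; power 81.3% at 120.
- Simulated log-rank power at 120: 81.7%.

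The stated 120 and 80% therefore reproduce.

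**3. Illustration of dilution.** Assumptions that are not in the documents: a share q of patients in both arms is counted early because of jaundice present at entry, with exponential time of mean 0.5 month, and the true rates are 50% and 25%. The observed 6-month rate is q + (1 − q) × true rate.

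- q = 5%: control 0.05 + 0.95 × 0.50 = 52.5%; RFA 0.05 + 0.95 × 0.25 = 28.75%. Hazard ratio implied by these rates: ln(0.7125)/ln(0.475) = 0.46. Simulated log-rank power is about 75%.
- q = 10%: control 0.10 + 0.90 × 0.50 = 55%; RFA 0.10 + 0.90 × 0.25 = 32.5%. Implied hazard ratio: ln(0.675)/ln(0.45) = 0.49. Simulated power is about 67%.

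A comparison of 6-month proportions, which does not depend on when the early events occur, gives about 76% and 70% for the same two shares, against about 82% at q = 0. The simulations used 6,000 runs each and the log-rank test on which the sample size was based, not the planned frailty model.

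**The case against.** The strongest reply is that the section titled Endpoint definition governs and Table 2 is schedule shorthand. Under that section residual jaundice alone is not an event: it must also lead to early stent replacement or disrupted chemotherapy, and the text on secondary endpoints repeats this for the event rate. The abstract already asks for an increase. All possible events go to a blinded, independent review committee, whose working rules a journal article would not normally print. Some patients enter at first stent replacement, so not all have undrained obstruction.

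Much of this stands. A reader might infer that any patient who enters above 5 mg/dl becomes an event at an early blood test. The documents do not support that for the endpoint section. They also schedule no laboratory tests between visit 1 and month 3, so earlier values would come from routine care. A reader might also infer that bilirubin is nowhere linked to a starting value; the abstract's wording contradicts that, although it names no reference.

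The reply does not remove the problem. The consequence clause still admits jaundice present at entry when chemotherapy is disrupted because of it. Those decisions are made by investigators who know the allocation. Blinded review applies a definition and cannot choose between three, none of which states a bilirubin reference.

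**Conclusion.** The point holds as an inconsistency in the definition of the only confirmatory endpoint, with a bilirubin criterion whose reference is not fixed. It changes which events count, so it is more than an editorial matter.

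The size of the effect cannot be taken from the documents. The relevant share is narrower than the share entering above 5 mg/dl: under the endpoint section it is those who remain above it, have a consequence because of it, and pass committee review. The falls to about 75% and 67% are conditional on assumed shares of 5% and 10%, equal in both arms. If RFA itself affected early drainage, the shares would differ between arms and the effect would not be simple dilution.

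A reader might infer that 120 patients are too few or that the stated power is wrong. Neither follows, because the stated hazard ratio, sample size and power all reproduce. Larger assumed shares give larger losses, but nothing in the documents supports them.

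**What to change.** 1. Use one definition in the abstract, in Endpoint definition and in Table 2 footnotes e and h. Keep the consequence clause, and say that it covers the bilirubin part as well as cholangitis.
2. Make the bilirubin part an increase to above 5 mg/dl, as the abstract already has it, against a stated reference. One option is the lowest recorded value from baseline onward, including routine-care values entered in the eCRF. A value still falling from a raised baseline is then not an event.
3. State in advance how patients who never fall to 5 mg/dl or below are classified (primary drainage failure), and report the analysis both with and without them as events. Those with early stent replacement or disrupted chemotherapy have an outcome that the protocol treats as important, so they should not leave the primary analysis without justification.

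The cost is revised wording, updated rules for the endpoint review committee, and entry of routine interim bilirubin values in the eCRF. The last is real extra work, because the scheduled laboratory tests alone cannot supply a lowest value before month 3. The sample size calculation does not change. The revision should be in place before events are adjudicated.

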### Quality assurance and safety

Patient data will be collected in electronic case report forms (CRF). Three independent experts will be appointed to serve as an Independent Data Monitoring Committee (IDMC) and give expert advice and supervision entirely independent of the applicants and the medical institutions involved. The IDMC will conduct thorough safety assessments throughout the study and will review all RFA-related events and decide on trial continuation after every 10th RFA procedure. A “harm rate” of ≥ 20% (≥ 6 RFA-related grade ≥ 4 events among the first 30 patients in the intervention group) will be suggested to the IDMC as critical.

The ERC will be responsible to blindly review and to verify countable events in both study arms to reduce possible biases caused by lack of blinding of the investigators to the RFA procedure. In addition, regular monitoring visits will be conducted by the AIO-Studien-gGmbH to ensure protocol adherence of the sites. A safety event (adverse event (AE) as per ICH-good clinical practice (GCP)) is defined as any untoward medical occurrence or experience in a subject or clinical investigation subject. Worsening of a pre-existing medical condition (e.g. diabetes, migraine headaches, gout) will be considered a safety event if there is either an increase in severity, frequency, or an association with significantly worse outcomes. A possible safety event will be graded according to CTCAE v5 and will be reviewed by the investigator and is properly captured in the subjects’ medical records and the electronic CRF. CTCAE grade 1 and 2 will only be regarded a safety event, if judged as “clinically relevant” by the investigator or if interfering with treatment administration. CTCAE grade 3 and 4 will always be regarded as safety events.

### Sample size calculation and statistical analysis

The sample size of 120, i.e., 60 patients per group, was calculated based on the two-sided log-rank test for time to first event analysis. Thereby, a power of 80% can be reached under the following assumptions and with a two-sided significance level of 5%. Based on previous reports [7, 9, 14, 20], the event rate at 6 months in the control group was estimated to be 50% and 25% in the intervention group resulting in a hazard ratio (HR) of 0.415. The follow-up will be fixed at 6 months. Furthermore, it was assumed that there will be a low loss to follow-up of 2.5% over six months and all patients stay within their treatment group within the observational period. PASS version 16.0.3 was used for the calculation of the sample size.

Descriptive analysis for baseline characteristics will be performed giving mean, standard deviation, median, and inter-quantile range for continuous data as well as counts and percentages for categorical data. Tests of statistical significance will not be undertaken for baseline characteristics; rather the clinical importance of any imbalance will be noted [22]. A modified ITT (mITT) population will be used for the primary endpoint analysis. The mITT population consists of all patients who will be randomized in the ACTICCA-2 trial and who will undergo endoscopic stenting.

Primary endpoint analysis will be conducted using a cause-specific Cox proportional hazards model comparing the two treatment groups regarding time to first event within 6 months with trial site as random effect (frailty) and tumor location (perihilar vs. ductal) and stent material (plastic vs. metallic) as fixed effects. An adjusted HR for the treatment effect with corresponding 95% CI and p-value will be given as well as cumulative incidences with 95% CIs. The secondary endpoint OS will be analyzed with the Cox proportional hazards model with a frailty for trial site and adjusting for stratification variable tumor location and the variable stent material. Mixed models will be used for further secondary endpoints (linear, logistic, or negative binomial as appropriate).

The mITT population will also be used for the secondary endpoint analysis. As a sensitivity analysis for the primary event of interest, results of the model by Fine and Gray will be given to take the competing event “death” into account. Cause-specific time-to-event analysis will be conducted for the components of the primary endpoint. Explorative subgroup analyses will be conducted in the same manner as for the primary outcome. Further sensitivity analysis will be conducted for the primary outcome, i.e., analysis for the per protocol population. The per protocol population includes all patients without major protocol violations. Furthermore, safety analyses will be conducted by the ERC/IDMC throughout the trial to decide about trial continuation after every 10th RFA procedure. Interim analyses are not planned. Missing values will not be imputed. Only the primary endpoint is analyzed in confirmatory manner with a two-sided significance level of 5% and all other analysis are considered explorative. Hence, no adjustment for multiple testing is conducted. A detailed statistical analyses plan will be prepared and finalized before the randomization code is broken. Data will be analyzed according to the Consolidated Standards of Reporting Trials (CONSORT) statement [23]. Statistical analyses will be carried out with an established statistical software such as SAS (Cary: SAS Institute Inc.; 2013.), Stata (College Station: StataCorp LLC.; 2021), R (Vienna: R Foundation for Statistical Computing; 2023.), or SPSS (Armonk: IBM Corp; 2021.).

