No concomitant disease or malignancy interfering with the study procedure or efficacy outcome measures, particularly no severe or uncontrolled cardiovascular disease (congestive heart failure NYHA III or IV, unstable angina pectoris, myocardial infarction within ≤ 3 months, significant arrhythmias) and no psychiatric disorders precluding understanding of information of trial related topics and giving informed consent

*CCA*: cholangiocarcinoma, *ECOG*: Eastern Cooperative Oncology Group, *RFA*: radio frequency ablation, *NYHA*: New York Heart Association Functional Classification, *MDT*: multidisciplinary team

Randomization to study treatment should occur within three weeks after eligibility criteria have been met. Study subjects will be randomized by the electronic CRF to arm A (intervention group) or B (control group) in 1:1 ratio, stratified by trial site and tumor location (perihilar vs. ductal). The procedure itself (i.e., endoscopic stenting with or without RFA) and randomization are on the same day.

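### Primary and secondary analyses are restricted to randomised patients who are actually stented, a post-randomisation condition that RFA can affect in arm A only

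*Protocol article*

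**What the plan says.** The section on sample size and statistical analysis defines the modified intention-to-treat (mITT) population for the primary endpoint: "The mITT population consists of all patients who will be randomized in the ACTICCA-2 trial and who will undergo endoscopic stenting". The abstract uses the past tense, so actual stenting decides membership, not the intention to stent: "All patients who are randomized and who underwent endoscopic stenting will be used for the primary endpoint analysis".

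The same section extends this set: "The mITT population will also be used for the secondary endpoint analysis". The endpoint section lists what that covers: "The secondary endpoints will include OS, QoL, clinical event rate at 6 months, total days of over-night-hospital-stays during the trial period as well as safety".

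Three design features matter here:
- In arm A the ablation is done "employing a CE-certified RFA-catheter prior to stent placement". Arm B has no corresponding step.
- On timing: "The procedure itself (i.e., endoscopic stenting with or without RFA) and randomization are on the same day".
- On blinding: "ACTICCA-2 is a multicenter, randomized, controlled, open-label, investigator-initiated trial".

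The only other population named for the primary outcome is per protocol: "Further sensitivity analysis will be conducted for the primary outcome, i.e., analysis for the per protocol population". A Fine and Gray model is also planned, but it changes the model and not the population.

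**The concern.** Leaving out patients who never receive the study procedure is defensible when the exclusion cannot depend on the allocated arm. Here it can. Stent placement follows randomisation, the endoscopist knows the arm, and arm A has an extra step before the stent. A patient with an RFA complication after which no stent is placed leaves the RFA arm of the analysis, and no control patient can leave by that route.

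Such patients had an indication for drainage and did not get it by stent, so they are plausibly at higher risk of jaundice, cholangitis, interrupted chemotherapy and death. If so, dropping them flatters RFA in the one confirmatory test. It does so more plainly in OS, because a death can be observed whether or not there is a stent, and in the between-arm safety comparison, which the article calls a major aim. The blinded endpoint review does not help: it judges events, not who belongs to the analysis set.

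**Working it through.** **Step 1: the plan's own figures.** Inputs from the sample size section: 60 per arm, 6-month event rates 50% and 25%, two-sided 5%, 2.5% loss, fixed 6-month follow-up.

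- HR = ln(1 − 0.25) / ln(1 − 0.50) = 0.2877 / 0.6931 = 0.415, as stated.
- Expected events with exponential event and loss hazards λ and η: 60 × λ/(λ+η) × (1 − exp(−6(λ+η))) per arm, which gives 29.7 + 14.8 = 44.5.
- Freedman: z = √44.5 × (1 − 0.415)/(1 + 0.415) − 1.96 = 0.80, power 78.7%. Lakatos gives 81.3%, Schoenfeld 83.5%, and simulation (10,000 runs) 82.2%.

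The stated 80% reproduces, so the sample size is not in question.

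**Step 2: bias when RFA has no effect.** The documents give no rate of randomised patients left without a stent, so k is an assumption. Suppose 30 of 60 would fail in each arm, k of the 30 in arm A are unstented and dropped, and none is dropped in arm B.

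Apparent RFA risk p = (30 − k)/(60 − k); apparent HR = ln(1 − p)/ln(0.5). The last column is the simulated chance that a two-sided 5% log-rank test declares RFA superior (6,000 runs per row; nominal 2.5% in that direction).

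| k | p | Apparent HR | False win for RFA |
|---|---|---|---|
| 0 | 30/60 = 50.0% | 1.00 | 2.9% |
| 1 | 29/59 = 49.2% | 0.98 | 3.2% |
| 2 | 28/58 = 48.3% | 0.95 | 3.8% |
| 3 | 27/57 = 47.4% | 0.93 | 4.5% |
| 4 | 26/56 = 46.4% | 0.90 | 5.5% |
| 6 | 24/54 = 44.4% | 0.85 | 8.8% |

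The simulation error on the first row is about √(0.029 × 0.971/6000) = 0.2 percentage points.

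**Step 3: what the set hides when RFA works as planned.** Let stented RFA patients have the planned 25% risk, and let the k unstented ones all count as failures. The mITT analysis still targets 25%, HR 0.415 and a number needed to treat (NNT) of 4, whatever k is. Over all 60, the RFA risk is (k + 0.25 × (60 − k))/60.

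| k | RFA risk, all 60 | Risk difference (points) | NNT |
|---|---|---|---|
| 1 | 26.3% | 23.8 | 4.2 |
| 2 | 27.5% | 22.5 | 4.4 |
| 3 | 28.8% | 21.3 | 4.7 |
| 4 | 30.0% | 20.0 | 5.0 |
| 6 | 32.5% | 17.5 | 5.7 |

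**Step 4: would an ITT label alone be enough?** No, for two reasons in the text. The primary and OS Cox models adjust for stent material, which an unstented patient does not have, and missing values are not imputed, so the fitted models would drop the same patients again. And the primary event is defined as stent dysfunction, which has no stated meaning for a patient without a stent.

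**The case against.** Much of the opposing case stands, and it limits what may be claimed.

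- **Interrupted sessions.** A reader might infer that any RFA problem that stops the index session deletes the patient. The text sets no time limit on stenting, so a patient stented at a later session still qualifies, and a failed RFA passage need not prevent stenting. The loss requires that no stent is placed at all.
- **Both arms.** A reader might infer that exclusions occur in arm A only. Stenting can fail in arm B too. If equal numbers of would-be failures left both arms, say 27/57 remaining in each, the HR under no effect would be 1. Only exclusions caused by RFA are one-sided.
- **Size.** The background section's pooled figures do not point to many extra exclusions. Hemobilia is 4.3% with RFA and 3.2% with stent only, or (0.043 − 0.032) × 60 = 0.7 patients per arm, and cholangitis is lower with RFA (9.5% against 15.5%). The early series there look worse (3 biliary bleeds and 3 severe cholangitis cases among 12 patients), but none is reported as having prevented stenting.
- **Primary failures.** Perforation or bleeding is not a primary event, and death is treated as competing. A reader might infer that an excluded procedural death is a lost primary event; it is lost from OS and safety instead.
- **Safety.** A reader might infer that the worst RFA complications vanish. The quality assurance section has the monitoring committee review all RFA-related events, with no restriction to the mITT set. What is exposed is the planned between-arm comparison.

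A supplementary all-randomised analysis or a separate safety set could appear in the analysis plan, and its absence from an article would not by itself be a finding. But the article does not merely omit a set: it fixes the confirmatory and secondary set by a post-randomisation condition.

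**Conclusion.** The concern holds as a defect in the stated analysis set. Membership depends on actual stenting, which comes after open-label randomisation and which RFA can prevent in arm A by a route that arm B lacks.

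The size is unknown because no non-stenting rate is given. Under no true effect, with all k exclusions in arm A and all of them would-be failures, the apparent HR moves only to 0.98-0.95 for one or two patients, but to 0.90-0.85 for four to six, where the false-win rate is about 5.5-8.8%. The direction favours RFA if the dropped patients do poorly. OS and comparative safety are exposed most directly.

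The documents do not support saying that the result will be biased by any particular amount, that exclusions will be confined to arm A, or that serious RFA events escape monitoring.

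**What to change.** 1. Define the primary and OS analyses on all randomised patients, in the allocated arm, with time counted from randomisation.
2. State in advance how a patient without a stent counts for the primary endpoint, for example bilirubin above 5 mg/dl or cholangitis that leads to a biliary re-intervention or disrupts chemotherapy.
3. Remove stent material from the primary and OS models, or replace it with the stent type planned before randomisation, so that unstented patients stay in the fit.
4. Keep the stented set as a sensitivity analysis.
5. Base the safety comparison on every patient in whom the index ERCP was started.
6. Report unstented patients by arm, with reasons.

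The cost is mainly wording in the protocol and analysis plan, plus recording planned stent type before randomisation if that option is chosen. A few unstented patients should dilute the effect only slightly. The extreme case is larger: if the planned effect holds in stented patients and every unstented patient is in arm A and fails on day 0, simulated power falls from about 82% to about 77%, 70%, 63%, 54% and 38% for k = 1, 2, 3, 4 and 6. That loss reflects a smaller benefit in the patients randomised to RFA, which the stented set would conceal.
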